## Methods

### Study Objectives

The primary objective of the EZI-PrEP study is to assess whether online-mediated PrEP care is noninferior to standard in-clinic care and whether monitoring every 6 months is noninferior to standard monitoring every 3 months. We defined the primary outcome measure as a condomless anal sex act with a casual partner during which PrEP was not used or insufficiently used (herein referred to as an “unprotected act”). Ideally, incident HIV infection would be the primary outcome, but this outcome is expected to be exceedingly rare for use in a clinical trial [42]. The outcome “unprotected act” can be regarded as a behavior that carries the most risk for HIV acquisition and is expected to occur frequently enough to serve as the primary outcome.

The secondary objective is to compare differences between PrEP care modalities in the incidences of bacterial STIs (ie, chlamydia, gonorrhea, and syphilis), HIV infection, and HCV infection; intracellular concentrations of TFV-DP; retention in PrEP care; total number of STI consultations (in addition to PrEP monitoring visits); and satisfaction, usability, perceived quality, acceptability, and time and cost investments of PrEP care.

Furthermore, to investigate how suitable the offered PrEP care modalities are for participants, we will study the associations of the sociodemographic, behavioral, and psychosocial predictors of PrEP adherence with all outcomes mentioned above, and assess whether these associations vary between study arms. More specifically, we will study the associations of unprotected acts with problematic alcohol and drug use, risk perception of acquiring STIs and HIV infection, and sexual compulsivity. Adequate PrEP adherence is key to its effectiveness in preventing HIV, and regular PrEP adherence counseling is therefore recommended. While ample evidence exists on the facilitators and barriers of medication adherence across different populations and settings [43] (eg, medication for the prevention and treatment of cardiovascular diseases [44], chronic disease management [45], and HIV treatment [46]), this remains an understudied topic for MSM who use PrEP. We are interested in how PrEP intake is integrated in daily life, what circumstances may lead to inadequate PrEP adherence, and whether these factors are associated with fewer contact moments between health care providers and PrEP users. We will therefore study the relationship between habit formation and PrEP intake. We will also analyze mental well-being (eg, positive and negative emotions, depression, stress, and anxiety) in relation to adherence and unprotected acts, and explore the mediating effects of personality-related variables (eg, emotion regulation, coping skills, conscientiousness, and resilience). Finally, we will investigate to what extent having a social environment, which is measured by social norms, loneliness, and support systems, is related to PrEP adherence and retention in PrEP care.

### Study Setting

The EZI-PrEP study will be embedded in the government-funded National PrEP Pilot Program (NPP) that plans to run from August 2019 until July 2024 [47]. This program provides PrEP care to persons at high risk for HIV infection, notably MSM and TGDP, and is implemented by the sexual health centers (SHCs) of the public health service (PHS) regions throughout the Netherlands. The PrEP care offered consists of in-clinic monitoring visits every 3 months that are free of charge. PrEP tablets are provided at a reduced price of €7.50 (US $7.88) per 30 tablets (paid out-of-pocket by the PrEP user) and are provided only to those completing a monitoring visit. Following the Dutch PrEP guidelines applicable at the time when the study started (ie, April 15, 2019 [10]), each PrEP monitoring visit includes screening for HIV infection, bacterial STIs, and HCV infection, and, every 6 months, screening for kidney function (Table 1). It also includes counseling based on motivational interviewing techniques to stimulate informed and conscious decision-making by PrEP users in relation to their own sexual health, PrEP intake, and usage of other HIV-prevention strategies. PrEP naïve people are allowed to commence PrEP immediately after screening and counseling, and have to return to the SHC after the first month of PrEP use for repeat HIV testing. Three months after commencing PrEP, routine PrEP care begins with the first in-clinic monitoring visit (performed every 3 months). Individuals are allowed to test for HIV, STIs, and HCV free of charge in between regular PrEP monitoring visits at their own initiative. Individuals can freely choose and switch between daily or event-driven PrEP regimens. These guidelines have since been updated in 2022, with the most relevant modification being that the monitoring frequency may be adapted under certain individual cases [11].

**Table 1 table1:** Overview of testing for HIV infection, sexually transmitted infections, hepatitis C virus infection, and kidney function as part of routine pre-exposure prophylaxis care for each EZI-PrEP study visit at sexual health centers in the Netherlands (based on Dutch national pre-exposure prophylaxis guidelines; April 19, 2019).

Laboratory measurement	Inclusion	Months								
		1	3	6	9	12	15	18	21	24
HIV	✓	✓^a^	✓	✓	✓	✓	✓	✓	✓	✓
Syphilis	✓		✓	✓	✓	✓	✓	✓	✓	✓
*Chlamydia trachomatis*	✓		✓	✓	✓	✓	✓	✓	✓	✓
*Neisseria gonorrhoeae*	✓		✓	✓	✓	✓	✓	✓	✓	✓
HCV^b^	✓		✓	✓	✓	✓	✓	✓	✓	✓
Creatinine	✓			✓		✓		✓		✓
Proteinuria	✓			✓		✓		✓		✓

^a^Only pre-exposure prophylaxis starters and restarters have a pre-exposure prophylaxis monitoring visit at month 1.

^b^HCV: hepatitis C virus.

In the Netherlands, PrEP can also be obtained through a general practitioner, although, in this instance, neither PrEP tablets nor laboratory testing are fully reimbursed by the Dutch health insurance. The Dutch insurance system has an obligatory deductible excess, meaning that the first €385 (US $404) of health care costs, including laboratory testing ordered by primary care providers, are paid for out-of-pocket. Moreover, knowledge and willingness to prescribe PrEP varies across general practitioners. Most people who are using or want to use PrEP in the Netherlands therefore procure PrEP through the NPP. This program has been capped at 8500 PrEP users, which has resulted in individuals being placed on waiting lists to obtain PrEP from the NPP [24].

### Study Design

The EZI-PrEP study will be a 2×2 factorial, 4-arm, open-label, multi-center, randomized, controlled, noninferiority trial. Study participants will be randomized to 1 of 4 arms: (1) in-clinic monitoring every 3 months (standard of care), (2) in-clinic monitoring every 6 months, (3) online monitoring every 3 months, or (4) online monitoring every 6 months (Figure 1). The study will be implemented at SHCs in Amsterdam, Rotterdam-Rijnmond, Haaglanden, and Gelderland-Zuid (Figure 2). For each individual participant, the planned observation time is 24 months, starting after eligibility screening and enrollment.

All study participants will receive access to a smartphone app (the “EZI-PrEP app”), which contains a diary. Participants will be required to complete this diary daily during the first 18 months of the study period. This information will be used to measure the primary outcome (ie, unprotected acts). DBSs will be collected at months 6 and 12. Routine clinical data registered during PrEP monitoring visits and any additional STI testing or treatment visits from inclusion until the final monitoring visit at month 24 will be retrieved from the national STI surveillance system. Participants will be requested to complete 5 questionnaires (at baseline and at 6, 12, 18, and 24 months) to collect data on PrEP intake; sexual behavior; psychosocial characteristics; and the experiences, acceptability, and usability of the interventions. We will extract automatically registered data on app usage from the app.

**Figure 1 figure1:**
[figure not shown]
EZI-PrEP study flowchart. DBS: dried blood spot; EZI-PrEP: E-Health for Zero Infections - facilitating access to and use of Pre-Exposure Prophylaxis in the Netherlands; PrEP: pre-exposure prophylaxis; SHC: sexual health center.

**Figure 2 figure2:**
[figure not shown]
Map of the Netherlands with EZI-PrEP study sites. EZI-PrEP: E-Health for Zero Infections - facilitating access to and use of Pre-Exposure Prophylaxis in the Netherlands; PHS: public health service.

### Study Population

We aim to include 442 individuals who are already using PrEP through the Dutch NPP or will be starting or restarting PrEP. Individuals starting PrEP are PrEP naïve (herein referred to as “PrEP starters”), whereas individuals restarting PrEP are persons who have used PrEP more than 6 months prior to inclusion and will recommence PrEP at inclusion (herein referred to as “PrEP restarters”). Both groups of individuals need to have a monitoring consultation after 1 month of starting or restarting PrEP as part of standard-of-care procedures and are therefore grouped in the protocol as “PrEP starters or restarters.” Our intention is that at least 25% of study participants will be PrEP starters or restarters.

The eligibility criteria will be as follows: (1) being eligible for the Dutch NPP (Textbox 1) [45]; (2) being 18 years or older; (3) living in the catchment area of a participating PHS; (4) being able to complete informed consent, medical history, the daily diary, and questionnaires in English or Dutch; (5) having an email address; (6) owning an iOS or Android mobile phone capable of running the study app; (7) having daily access to an internet connection; (8) being able to make online payments; and (9) providing informed consent. The exclusion criteria will be as follows: (1) having an HIV infection; (2) being advised by a physician to wait with starting or restarting PrEP (PrEP starters or restarters) or being advised to stop with PrEP (current PrEP users) for more than 1 month, such as in the case of decreased kidney function with an estimated glomerular filtration rate (eGFR) of less than 60 mL/min/1.73m^2^ or other kidney problems, or chronic use of medication that interacts with TFV/FTC; (3) being advised to have in-clinic monitoring every 3 months, such as in the case of adverse mental health conditions or life circumstances, chronic or acute hepatitis B virus infection, or other medical conditions that require special attention when using PrEP or may need a referral, such as osteoporosis or other bone diseases; and (4) participating in another clinical trial or research project related to HIV prevention.

Eligibility criteria of the Dutch national pre-exposure prophylaxis pilot program (Dutch national pre-exposure prophylaxis guidelines dated April 15, 2019).Men who have sex with men or transgender and gender diverse people who in the 6 months prior to the pre-exposure prophylaxis (PrEP) request or PrEP consultation:Had anal sexual intercourse without a condom with a male partner having an unknown HIV statusHad anal sexual intercourse without a condom with a male partner having a known HIV-positive status and a detectable viral loadWas diagnosed with a rectal sexually transmitted infection or syphilisReceived a prescription for HIV postexposure prophylaxis

### Recruitment

We will recruit participants mainly at the SHCs of the participating PHSs. Current PrEP users will be recruited during regular PrEP monitoring visits by a health professional (usually a nurse or a physician). Individuals who are starting or restarting PrEP will be recruited from the waiting lists for PrEP care via email, SMS text messaging, or a phone call and routine communication channels of the respective SHC. The enrollment visit will be scheduled together with the first PrEP consultation. To support the recruitment efforts of the SHCs, we developed a website [48] and promotional materials for distribution to SHC clients. In addition, depending on the recruitment rate in the participating SHCs, we plan to conduct 3 advertising rounds on the MSM dating platform Grindr, targeting potential participants living in the catchment areas of the 4 participating PHSs. All promotional materials and advertisements will link to the EZI-PrEP website page with a short application form.

### Enrollment Procedures

In preparation of the enrollment visit, potential participants will receive an email with the patient information folder and will be asked to download the EZI-PrEP study app. The enrollment interview will begin with a regular PrEP consultation at the SHCs, which will be combined with eligibility screening (Figure 1). Noneligible individuals will continue or commence routine PrEP care. Eligible individuals will be guided through study procedures and asked to sign an informed consent form, and will be subsequently randomized to 1 of the study arms. Each participant will then onboard the EZI-PrEP app and complete the diary for that day to ensure understanding of the questions asked in the diary. This first diary entry will not be used for analysis because it is completed in the presence of a health care worker. The enrollment interview will be finalized with scheduling of the next monitoring appointment and PrEP provision.

The Dutch PrEP guidelines allow for combining STI and HIV test specimen collection with PrEP dispensing, as long as a client can be easily reached to communicate HIV and STI test results [10,11]. In case of a positive HIV test result, the PrEP user will be notified immediately to discontinue their PrEP and will be referred to HIV care. This strategy may lead to postrandomization exclusion from the EZI-PrEP study within 1 week after randomization.

### Randomization

Participants will be randomized (stratified by PHS and by PrEP experience, that is, those starting or restarting PrEP, and current PrEP users) to 1 of 4 study arms in permuted blocks of 4. Randomization will be performed by a statistician of PHS Amsterdam who is not part of the EZI-PrEP study team at initiation of the study, using Stata Intercooled 15.1 (StataCorp). Sequentially numbered and colored nontransparent envelopes will be made, containing a code for the study arm. Each PHS will receive 2 sets of envelopes, red ones for those starting or restarting PrEP and blue ones for current PrEP users. During the enrollment interview, in the presence of the participant and dependent on their PrEP experience, the health care provider will open the next envelope to reveal the study arm and study number.

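### A single block length of 4 for 4 arms lets site staff who know it and the earlier allocations deduce every fourth arm in an envelope set

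*Protocol article*

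**What the plan says.** All references are to the protocol article.

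- **Block length (Randomization).** Participants are assigned "to 1 of 4 study arms in permuted blocks of 4". No other length is given, and nothing says that the length varies or is withheld from the sites.
- **Strata (Randomization; Study Design).** The list is "stratified by PHS and by PrEP experience, that is, those starting or restarting PrEP, and current PrEP users". With four sites this makes 4 × 2 = 8 separate sequences.
- **Envelopes (Randomization).** "Sequentially numbered and colored nontransparent envelopes will be made, containing a code for the study arm". Every site holds two such sets, told apart by colour, one for each PrEP-experience group.
- **Opening (Randomization).** At the enrollment interview, with the participant present, "the health care provider will open the next envelope to reveal the study arm and study number".
- **Blinding (Study Design).** The trial is a "2×2 factorial, 4-arm, open-label, multi-center, randomized, controlled, noninferiority trial".
- **Order of steps (Enrollment Procedures).** The interview starts with a PrEP consultation that includes eligibility screening. Signed consent follows, then randomization.
- **Discretionary criterion (Study Population).** Exclusion 3 removes anyone "being advised to have in-clinic monitoring every 3 months, such as in the case of adverse mental health conditions or life circumstances".
- **Visibility of past allocations (EZI-PrEP Administration Portal).** Accounts are set up according to arm, and staff can open those of participants at their own centre.
- **Safeguards stated (Randomization).** A statistician outside the study team produces the list, and the envelopes are opaque.

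**The concern.** An opaque envelope hides its contents only while they cannot be worked out from what came before. When the block length equals the number of arms, the last envelope of each block is fixed by the three before it, and the third is down to two possibilities. The open-label design, the sequential numbering and one colour per stratum make the position within a block easy to follow.

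This matters because the eligibility decision contains a judgement. Exclusion 3 asks whether a person should have in-clinic care every 3 months, which is the schedule of arm 1. Someone who expects the next envelope to give an online or 6-monthly arm could, in good faith, apply that exclusion more readily to a less stable client than when expecting arm 1. Experimental slots would then be filled by a somewhat more selected group. The primary analysis uses crude incidence rate ratios (Primary Outcome), so it takes no account of such differences. The Discussion also relies on randomization when it argues that diary effects should not differ between arms.

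**Working it through.** The article gives no predictability figure, so there is none to reproduce.

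**Inputs.** 4 arms, block length 4 and 8 strata (Randomization, Study Design); planned total 442 (Power and Sample Size Calculation). Assumption: the observer knows the block length and all earlier allocations in the same envelope set.

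**1. Arm level.** At position *k* of a block, 5 − *k* arms remain, all equally likely, so the chance of a correct guess is 1/(5 − *k*).

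| Position | Correct arm guess | Arm certain |
|---|---|---|
| 1 | 1/4 | no |
| 2 | 1/3 | no |
| 3 | 1/2 | no |
| 4 | 1 | yes |

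Mean guess = (1/4 + 1/3 + 1/2 + 1)/4 = 0.521, against 0.25 if unpredictable. Certain share = 1/4 = 25%.

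**2. Number of participants.** If all blocks were complete, 442/4 = 110.5. If each of the 8 strata ended with three envelopes of an unfinished block, (442 − 8 × 3)/4 = 104.5. So about 105 to 110 participants would sit in a fully determined position.

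**3. Factor level.** The two primary comparisons are online versus in-clinic and 6- versus 3-monthly. For either, a block holds two slots of each level.

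- Position 1: guess 1/2.
- Position 2: three slots remain, two of them at the other level, so guess 2/3.
- Position 3: with probability 1/3 the first two slots had the same level and the rest is certain; otherwise the guess is 1/2. Mean = 1/3 × 1 + 2/3 × 1/2 = 2/3.
- Position 4: always certain.

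Mean guess = (1/2 + 2/3 + 2/3 + 1)/4 = 0.708, against 0.50. Certain share = (0 + 0 + 1/3 + 1)/4 = 1/3. Predictability is therefore higher for the comparisons actually tested than the 25% arm figure suggests.

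**4. Effect of changing the block lengths.** Fixed lengths were worked out exactly. Random lengths were simulated in sequences of 56 allocations (442/8 ≈ 55 per stratum), with each length equally likely and an observer who knows the set of possible lengths and all past allocations, but not the length of each block.

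| Scheme | Arm certain | Mean arm guess |
|---|---|---|
| Fixed 4 (plan) | 25% | 52% |
| Fixed 8 | 14% | 47% |
| Fixed 12 | 10% | 44% |
| Random 4/8 | about 7% | about 48% |
| Random 8/12 | about 4% | about 45% |
| Random 4/8/12 | about 3% | about 46% |

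Under random 4/8/12 the mean factor-level guess falls from 71% to about 66%. Varying the lengths removes most of the certainty but much less of the advantage in guessing.

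**The case against.** The strongest reply is that 25% is a ceiling. It requires someone at the site to know or infer the block length and to track three earlier allocations in one envelope set. The article does not say that sites are told the length. Recruitment is by nurses or physicians in general, not by one named recruiter, and reconstructing colleagues' allocations through the portal would take deliberate effort. This stands, and it is why the point is conditional.

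Three stronger readings are tempting, and the article does not support them.

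- *That one person both screens and opens the envelope, and so knows every fourth arm.* Both steps fall within one enrollment interview, but the article does not say that the same person does both or has the needed knowledge.
- *That staff can time enrolment visits to suit a predicted arm.* Recruitment ties enrolment to regular monitoring visits for current users and to the first PrEP consultation for starters and restarters. No section gives the person opening the envelope control over this.
- *That the bias runs towards noninferiority.* Exclusion 3 takes a person out of the trial; it does not move them to another arm. Staff might also favour predicted online slots for clients who find visits hard to attend, which could push the other way.

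The sequence of screening, consent and then randomization is also a real safeguard, as are the outside statistician and opening in front of the participant. They protect against tampering. They do not stop the next arm being deduced while eligibility is still being judged.

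Finally, timing. Results expects the 24-month questionnaires to be complete by Fall 2024, which implies last enrolment around Fall 2022. Few or no envelopes may be left to replace.

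**Conclusion.** The point holds in conditional form. With a fixed block of 4 for 4 arms, a person who knows the block length and the earlier allocations in an envelope set can be certain of 25% of arms and 33% of factor levels, and guesses correctly on average 52% and 71% of the time. The open-label design and the arm-dependent portal accounts make that knowledge obtainable. The article shows neither that anyone had it nor that anyone acted on it. The consequence is a risk of selection bias, of unknown size and only possibly towards noninferiority, which the crude primary analysis does not address. It is a concealment weakness that is cheap to correct while envelopes remain, not evidence that the randomization failed.

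**What to change.** For envelopes not yet used:

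1. Generate the list with randomly varying block lengths, for example 4, 8 and 12, within the same 8 strata, and do not disclose the lengths to the sites.
2. Have the eligibility decision, explicitly including exclusion 3, irrevocably recorded before the envelope is taken. The article already places screening before randomization; what is added is a record that cannot be changed afterwards. This step is needed because varying lengths alone leave the best-guess arm rate at about 46%.

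The cost is a new list, new envelopes and slightly more possible imbalance in small strata when recruitment ends. The stratification stays as it is. If recruitment has closed, the results report should state the block length and whether site staff knew it, so that readers can judge the risk.

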### Interventions

#### PrEP Care Every 6 Months

Participants in arms 2 and 4 (Figure 1) will receive PrEP care every 6 months. All study participants, irrespective of study arm, will be allowed to get screened free of charge for HIV and STIs in between scheduled PrEP monitoring visits (eg, after a partner notification for an STI or in case of STI-related symptoms). To allow for monitoring in between testing, we will ask participants to visit the SHC where they receive PrEP care.

#### Online PrEP Care

Participants in arms 3 and 4 (Figure 1) will receive online-mediated PrEP care that mimics in-clinic PrEP care. Figure 3 depicts the process of online-mediated PrEP care. First, participants will access an established online HIV and STI test request platform for MSM called Testlab [49]. On this platform, participants will complete standard intake questions for a PrEP consultation. The number of PrEP tablets needed until the next monitoring date will also be reported. All medical information will be stored in the electronic patient files. Participants reporting STI symptoms at the scheduled online monitoring visit will be asked to visit the clinic for physical examination and treatment.

The participant will then receive a lab order from the Testlab platform to visit one of the connected laboratories to provide samples for HIV infection, STI, HCV infection, and kidney function testing (Table 1). Negative test results for HIV infection, STI, and HCV infection; normal kidney function test results; and positive test results for bacterial STIs will be communicated via the Testlab platform. Treatment of bacterial STIs will occur in the clinic at SHCs. In case of a positive test result for HIV or HCV, or a decreased kidney function, participants will receive a phone call to make an appointment on the same day.

To provide counseling on sexual well-being, PrEP intake, and other HIV prevention strategies, a video consultation will take place. These video consultations will become optional after 6 months. The continuation of video consultation will be based on shared decision-making between the participant and the SHC health care provider. Self-reported medical history and testing for HIV infection, STIs, HCV infection, and kidney function will remain mandatory for PrEP provision. For the purpose of the study, a mandatory video consultation will take place at 18 and 24 months to inform participants about study procedures that change at those time points (Figure 1).

Participants in the online arms may opt for home delivery of PrEP tablets, for which a service fee of €9.50 ($9.98) will be requested and will require an online payment. Pick up of PrEP tablets from the SHC will also be possible without any additional cost. The SHC physician will determine the number of tablets that a participant is able to obtain based on the intended PrEP regimen and the number of tablets requested by the participant in the self-reported medical history.

